*i-STAT validation in moving ambulance:*, A validation of the i-STAT POC troponin assay in a moving ambulance will be performed. Previous study of the Abbott i-STAT POC troponin device showed high correlation between results in a moving ambulance compared with a laboratory environment. However, this is a small study and local validation is required before our paramedics and ED physicians use POC troponin results to influence clinical care. The first step of the i-STAT device validation will be to measure QC samples in a moving ambulance. Next, we will validate whole blood samples from all 500 patients by comparing i-STAT and central lab troponin results. These patients will have testing from the same blood draw with the Abbott i-STAT troponin assay in the ambulance followed by testing with the central lab assay: AccuTnI+3 assay (Beckman Coulter, California) or TnI-Ultra assay (Siemens, Munich Germany). The assay will be considered validated if the agreement between POC and central values (on “elevated” or “normal” results) in QC and patient samples is excellent; as defined by a kappa value >0.74. Validation will be done concurrent with the pilot implementation. The central lab troponin measurement will be run on whole blood obtained at the same time as blood used for the prehospital i-STAT. Please see Appendix 2 for the WFBMC Laboratory purposed method validation and quality control plan.*HEART Score Implementation Pilot:* Prior to implementation, over 70 paramedics will be trained to use the Abbott i-STAT device for POC troponin analyses and to calculate a HEART Score. Educational sessions will train the paramedics to correctly identify subjects appropriate for inclusion in the pilot and to correctly calculate a HEART Score. The educational tools will include in-person teaching and may include self-learning. Similar teaching methods and modules that have been used in the HEART Pathway Implementation (PI [name]) will be used in these sessions. Training regarding use of the Abbott i-STAT device will be conducted by Abbott Laboratories Inc. trainers. This will include the proper storage, maintenance, and use of device cartridges, quality assurance checks, and the interpretation and reporting or results. In addition to initial training, Abbott will provide full training and competency support for 1 year. Training and competency events for all testing personnel will be conducted at start-up, at 6 months, and at 12 months. Documentation of training and competency will be completed. There is no intent to publish this quality control data.

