*Post-Hoc Analysis of Troponin Cut Points:* For the clinical pilot, paramedics will use a cut point of 0.08 ng/mL, which corresponds to the published 99^th^ percentile upper reference limit for the assay. However, following completion of the pilot we will analyze different troponin cut points (including 0.04 ng/mL) used alone or in combination with the HEART score to find the combination with the greatest accuracy (area under the curve in a receiver operator curve).

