**LINEARITY/AMR/REPORTABLE RANGE**

Analytical measurement range (AMR) verification includes 3 levels of calibration verification materials tested in triplicate.

- Reportable Range will be 0.00 to 35.00 ng/mL

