**PRECISION**

Level 1, level 2, and level 3 liquid QC tested 20 times on the same day.

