**Validation (Accuracy)**

- - - - 20 QC samples (level 1, 2, and 3) tested in a moving ambulance
- **Will occur concurrently with pilot implementation**

We will compare test samples between i-STAT and the Core Lab troponin method.

i-STAT tested from a FULL lithium heparin green top tube, collected in the field and tested immediately after collection. Blood will NOT be transferred from one collection container to another collection container. The SAME green top tube to be sent to the Core Lab for testing upon arrival to WFBH Emergency Department.

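### An elevated/normal kappa on fixed-level QC liquids is a poor test of motion bias in the i-STAT, and QC should be kept out of the patient kappa

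*Protocol*

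**What the plan says.** Protocol section D4 describes two steps. The first is "The first step of the i-STAT device validation will be to measure QC samples in a moving ambulance". The second reads "Next, we will validate whole blood samples from all 500 patients by comparing i-STAT and central lab troponin results". One acceptance rule covers both: the assay is validated if "agreement between POC and central values (on “elevated” or “normal” results) in QC and patient samples is excellent; as defined by a kappa value >0.74". D4 does not say whether the QC and patient kappas are computed separately or together.

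Attachment K2 gives the QC material. Under Validation (Accuracy) it is "20 QC samples (level 1, 2, and 3) tested in a moving ambulance". It is unclear whether 20 is the total or the number per level, and no concentration is given. Under Precision it is "Level 1, level 2, and level 3 liquid QC tested 20 times on the same day", with no mention of an ambulance and no acceptance limit. The linearity check reads "Analytical measurement range (AMR) verification includes 3 levels of calibration verification materials tested in triplicate", again without a limit or any mention of motion.

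Section F3 supplies the cut point: "paramedics will use a cut point of 0.08 ng/mL, which corresponds to the published 99^th^ percentile upper reference limit for the assay". K2 adds that "Reportable Range will be 0.00 to 35.00 ng/mL", so QC levels could lie almost anywhere relative to 0.08.

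**The concern.** Patient samples spread over a range of concentrations, so an elevated/normal kappa on them says something about agreement near the cut. QC liquids do not spread: each level is one concentration measured repeatedly. A reading changes class only if the ambulance moves it across 0.08 ng/mL. A proportional error that carries no level across the cut leaves kappa untouched, however large it is.

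This matters because the QC liquids allow the one comparison in the plan that stays on a single assay, moving versus not moving. In the patient samples, motion is mixed with the difference between two methods, and K2's own test limitations warn that absolute values can vary between methods. D4 calls local validation necessary before results influence care. A QC step that discards the numerical readings adds little to that decision. If its pairs were pooled with the patients, it could also hide poor patient agreement.

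**Working it through.** **Inputs.** From the protocol: threshold 0.74 (D4), cut point 0.08 ng/mL (F3), 500 patients (D4), 20 QC samples at three levels (K2). K2 also gives analytical sensitivity 0.02 ng/mL as two SDs at zero (SD 0.01), CV 20% at 0.07 and CV 10% at 0.10. Assumed: the QC levels, and the proportion of patients elevated. The 0.74 is a chosen threshold with no derivation, so there is no plan figure to reproduce.

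**Formula.** Kappa = (po - pe)/(1 - pe), where po is observed agreement and pe is chance agreement from the margins.

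**1. QC with every ambulance reading halved.** Central classes are taken from the nominal level, without random error. Both readings of 20 are shown: 20 per level (60) and 7/7/6 (20).

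| Assumed levels, ng/mL | Kappa, 60 samples | Kappa, 20 samples |
|---|---|---|
| 0.02 / 0.5 / 5 | 1.00 | 1.00 |
| 0.00 / 0.17 / 2 | 1.00 | 1.00 |
| 0.04 / 0.12 / 2 | 0.40 | 0.375 |
| 0.02 / 0.05 / 0.15 | 0.00 | 0.00 |
| 0.10 / 1 / 10 | 0.00 | 0.00 |
| 0.2 / 1 / 10 | undefined | undefined |

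Example, third row with 60 samples: 20 elevated on both, 20 elevated on central only, 20 normal on both. po = 40/60 = 0.667; pe = (20 x 40 + 40 x 20)/60² = 0.444; kappa = 0.222/0.556 = 0.40. The first row still gives 1.00 at one fifth of the true value. The fifth row is undefined with no bias at all, because every level is elevated on both methods.

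Halving therefore passes only if at least one level is at or below 0.08, at least one is above 0.16, and none lies between.

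**2. A sound device with the lowest level near the cut and two levels well above it.** At 0.07 the SD is 0.014, so P(reading > 0.08) = P(Z > 0.714) = 0.24. At 0.075, interpolating the SD to 0.0133, it is 0.35. With 40 elevated and 20 near-cut samples, 6 false elevations give kappa 0.757 and 7 give 0.712. With 13 and 7, 2 give 0.765 and 3 give 0.634. Binomial probabilities of failing:
- Level 0.07: 18% (60 samples), 22% (20 samples).
- Level 0.075: 60% (60 samples), 48% (20 samples).

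**3. Patient samples alone.** With 500 patients, 50 elevated (10%) and errors only from elevated to normal, 19 misses give kappa 0.746 and 20 give 0.730. The tolerated misses are 10/25, 19/50 and 35/100 at 5%, 10% and 20% elevated, that is 40%, 38% and 35%. Halving would fail the patient step only if more than about 35-40% of elevated patients lay between 0.08 and 0.16.

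**4. Pooling.** Take 500 patients, 10% elevated on each method, symmetric disagreement. pe = 0.1² + 0.9² = 0.82; kappa 0.70 means (1 - 0.70) x 0.18 x 500 = 27 discordant pairs.
- Add 13 elevated and 7 normal concordant QC pairs: po = 493/520 = 0.948; elevated margin 63/520 = 0.121, pe = 0.787; kappa = 0.161/0.213 = 0.756.
- Add 40 and 20: po = 533/560 = 0.952; margin 90/560 = 0.161, pe = 0.730; kappa = 0.222/0.270 = 0.821.
- A patient kappa of 0.60 (36 discordant) becomes 0.675 with 20 QC samples and 0.762 with 60.
- At 15% elevated, 0.70 becomes 0.738 with 20 (still failing) and 0.791 with 60.

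With one-directional misses at 10% elevated, pooling raises the tolerated number from 19/50 to 24/50 (20 QC) or 33/50 (60 QC).

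**5. What a quantitative comparison would deliver.** Six ambulance and 20 stationary replicates at an assumed CV of 8-10%: 95% half-width for percent bias = CV x sqrt(1/6 + 1/20) x 2.06, about 8-10 points. At a level of 0.02 with SD 0.01 (CV 50%) the same formula gives 48 points, so percent bias is unusable near zero. In absolute terms that is 0.01 x 0.465 x 2.06, about 0.01 ng/mL.

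**The case against.** Several points on the other side stand.

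- **QC levels are unknown.** A reader might infer that the QC step passes whatever motion does. The documents do not support that: with a level between 0.08 and 0.16 halving fails, and with all levels above 0.16 kappa is undefined, which is not a pass.
- **The patient step must also pass.** A reader might infer that the rule would declare a badly biased device validated. D4 names both sample types, so QC alone cannot do that. Aim 1 is also framed on patients' blood, with QC only a first step.
- **Pooling is one reading.** D4 describes successive steps. It leaves pooling open but does not plan it.
- **No bias from motion is documented.** K2 names suppressed results and quality check codes as the effect of motion. Halving is a stress test, not an expectation.
- **Other QC exists.** K2's individualized plan requires 20 days of successful liquid QC at the test site, so some standard of success is presumed. No limit is printed, and motion is not mentioned there.
- **The consequence in this pilot is limited.** Point-of-care results are not to guide care, D4 states no intent to publish the QC data, and the MACE accuracy analysis does not use this verdict.

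These points bound the concern without removing it. None supplies a numerical criterion for the ambulance QC, and none makes an elevated/normal kappa a graded measure of bias at three fixed levels.

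**Conclusion.** The concern holds as a decision rule badly matched to its material. On QC liquids the kappa is governed mainly by where the unstated levels sit relative to 0.08 ng/mL. It can be 1.00 under a large proportional bias, undefined, or below the threshold for a sound device. The only stated pass criterion for the moving-ambulance QC therefore says little about what motion does to the measurement.

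The sizes rest on assumptions: the QC levels tried, normal errors with K2's CVs for the near-cut case, and for pooling 10-15% of patients elevated and QC about two thirds elevated with full concordance. Pooling with 20 QC samples crosses 0.74 from 0.70 at 10% elevated but not at 15%; with 60 it does so at both.

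The change should be made because it is cheap and strengthens what Aim 1 can conclude. It does not affect the primary MACE analysis.

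**What to change.** In D4 and K2:

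1. Restrict the kappa criterion to the patient samples and compute it without QC results.
2. State the QC concentrations, and whether 20 is the total or the number per level.
3. Compare the ambulance replicates at each level with the replicates already planned under Precision, specifying that the latter are run stationary and on the same QC lot. Report the difference in means with its 95% CI (percent bias for levels well above the cut, ng/mL for a level near zero) and the ratio of SDs. Judge these against limits the laboratory sets beforehand.
4. Report the rate of suppressed results and check codes in the ambulance, since that is the motion effect K2 names.

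The cost is a wording change and a short calculation. No new runs are needed if lots match and the Precision runs are stationary, which K2 does not currently say. The downside is that the laboratory must commit to limits and the device can fail this step.

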## A2. Primary Hypotheses

- Paramedics using the HEART score and Abbott’s i-STAT^®^ point-of-care troponin assay in the pre-hospital setting will achieve 98% sensitivity and negative predictive value for MACE during the index visit and at 30 days in patients with symptoms concerning for ACS.
- Inter-rater reliability (kappa) for HEART scores calculated by ED physicians in a hospital setting and paramedics in the pre-hospital setting using Abbott’s i-STAT^®^ point-of-care troponin assay will exceed 0.60.

##

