**F. Statistical Plan**

F1. Overview

The primary concept of the PARA-HEART project is to evaluate whether paramedics can be taught to calculate a HEART score accurately with acceptable intra-observer reliability (when compared to ED physician assessments). This project is a clinical pilot study in order to generate data to support a larger and non-observational implementation. If we are able to show that these scores can be reliably predict MACE and agree with ED physicians assessments, then we can start using the HEART score in the pre-hospital setting to alter care and transport triage and destination plans.

F2. Sample Size and Power

The PARA-HEART project is a clinical pilot study in which we hope to demonstrate that paramedics are able to achieve 98% sensitivity for the detection of MACE. To achieve a sensitivity of 98% with a lower bound of the 95% confidence interval that exceeds 90% we will need at least 50 patients with MACE events. Assuming a 10% MACE rate among our chest pain population,[^4-7^](#_ENREF_4) to include 50 patients with adverse events we will need a total sample size of 500 patients.

F3. Analysis Plan and Statistical Methods

The percentage of patients identified by paramedics using the HEART Score with POC troponin testing as high- and low-risk, the sensitivity, specificity, and positive and negative predictive values, positive and negative likelihood ratios, and accuracy for MACE will be calculated. Corresponding 95% exact binomial confidence intervals will be computed.

The proportion of patients receiving objective cardiac stress testing, cardiac catheterization, myocardial infarction, or cardiac death during the index hospitalization will be estimated for subjects classified as high and low risk by ED physicians and compared with those classified as high and low risk by paramedic assessment. Cardiac-related ED visits and readmission to the hospital will be calculated at 30 day follow-up. LOS will be reported using descriptive statistics, including median and inter-quartile range as this outcome tends to have a nonparametric distribution.

HEART scores calculated by the blinded primary ED provider will be compared to the HEART scores obtained by the paramedics. Raw percent agreement and kappa scores will be determined to assess intra-observer reliability. A kappa of >0.75 will be defined as excellent agreement, 0.60-0.74 will be defined as acceptable agreement, and <0.59 will be defined as unacceptable agreement.

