**REFERENCE RANGE STUDY:**

Will compare i-STAT results on patients with normal Core Lab troponins to verify published reference range.

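### The ambulance i-STAT is called validated on kappa > 0.74 alone, which ignores the direction of disagreement and sets no limit on elevated troponins that read normal

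*Protocol*

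**What the plan says.** Protocol D4 (Pilot Design), in the part on validating the i-STAT in a moving ambulance, gives a reason for the exercise, a data source and a pass mark.

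- Reason: "local validation is required before our paramedics and ED physicians use POC troponin results to influence clinical care".
- Data: after QC samples have been run in a moving ambulance, "we will validate whole blood samples from all 500 patients by comparing i-STAT and central lab troponin results".
- Pass mark: "The assay will be considered validated if the agreement between POC and central values", classed as elevated or normal, "in QC and patient samples is excellent; as defined by a kappa value >0.74".

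The pass mark has no confidence bound and does not treat elevated and normal samples separately. K2 (Laboratory Method Validation and Quality Control) adds linearity, precision, QC in the ambulance and a reference range check. It sets no numeric limit for agreement or for missed elevations. The reference range check looks only at the centrally normal side: "Will compare i-STAT results on patients with normal Core Lab troponins to verify published reference range". F3 plans sensitivity, specificity and exact intervals, but for the HEART score against MACE and not for i-STAT against the central lab. F3 also fixes the i-STAT side of the table: "paramedics will use a cut point of 0.08 ng/mL". The central-lab cut point is not stated.

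**The concern.** The two kinds of disagreement do not have the same consequence. If the i-STAT reads normal when the central lab is elevated, the patient loses 1 or 2 HEART points (Table 1 in B1) and can fall to 3 or below, which is the low-risk group. A false elevation pushes the other way. For a tool meant to identify low-risk patients, the first error is the one to bound.

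Kappa does not separate the two. When few samples are elevated, the many agreeing normal pairs can keep kappa above the mark while a sizeable share of the elevated samples is missed. D4 links validation to later clinical use, so a pass says more than the statistic can support. This is not a detail left to a later analysis plan. D4 states a complete decision rule, and that rule is on a scale that does not measure the error of interest.

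**Working it through.** **Inputs**

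- Pass mark: kappa > 0.74 (D4).
- Pairs: n = 500 (D4).
- Share of samples elevated by central lab: not in the protocol. Assumed 10%, by analogy with F2 ("Assuming a 10% MACE rate among our chest pain population"), with 5–20% as the range and 30% as an extreme.
- False-elevated rate (i-STAT elevated among centrally normal samples): not in the protocol. Assumed 0 to 2%.

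The 0.74 mark is a convention with no calculation behind it, so there is no plan figure to reproduce. The 500 comes from the MACE sensitivity target in F2 and was not derived for this validation.

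**Formula**

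Let a = both elevated, b = i-STAT elevated only, c = central lab elevated only (missed), d = both normal.

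kappa = 2(ad − bc) / [(a + b)(b + d) + (a + c)(c + d)]

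**1. Direction.** With a = 33, b = 0, c = 17, d = 450, kappa = 2(33 × 450) / (33 × 450 + 50 × 467) = 29,700 / 38,200 = 0.777. Making the 17 discordant pairs false elevations (b = 17, c = 0) gives the same 0.777.

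**2. Misses tolerated, 50 of 500 elevated**

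| False-elevated (of 450) | Missed (of 50) | kappa | Result | One more miss |
|---|---|---|---|---|
| 0 | 19 (38%) | 27,900 / 37,400 = 0.746 | pass | 0.730, fail |
| 5 | 16 (32%) | 30,100 / 40,600 = 0.741 | pass | 0.726, fail |
| 9 | 13 (26%) | 32,400 / 43,400 = 0.747 | pass | 0.733, fail |

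In the first row raw agreement is (31 + 450) / 500 = 96.2%, while positive agreement is 31/50 = 62%, exact 95% CI 47.2% to 75.3%.

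**3. Chance of passing.** Each scenario uses 200,000 multinomial draws of 500 pairs and counts how often the observed kappa exceeds 0.74.

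Device that truly misses one third:

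| False-elevated rate | 5% elevated | 10% | 15% | 20% |
|---|---|---|---|---|
| 0 | 77% | 79% | 78% | 71% |
| 0.5% | 54% | 64% | 64% | 60% |
| 1% | 32% | 48% | 50% | 48% |
| 2% | 8% | 20% | 26% | 27% |

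At 30% elevated with no false-elevated results, the figure is 46%.

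Device that truly misses one quarter, 1% false-elevated: 62%, 87%, 94% and 96% at 5, 10, 15 and 20% elevated.

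**4. QC samples.** The rule covers these too. If one third of elevated QC samples were missed with none falsely elevated, kappa would be 8/11 = 0.73 with one of three levels elevated, or 8/14 = 0.57 with two of three. Both fail.

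**The case against.** A reader might infer that a device missing a third of elevated troponins would usually be passed. The documents do not support that without a condition. It needs false-elevated results of about 0.5% or fewer and 5–20% of samples elevated. At 1% false-elevated it is about even or worse, and at 2% the device usually fails. The protocol also gives grounds to expect errors in both directions. K2 puts the 20% and 10% imprecision levels at 0.07 and 0.10 ng/mL, either side of the 0.08 cut point, and says that partly clotted samples can read high. This objection stands, so every pass rate above is tied to its assumption.

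Second, the QC samples fall under the same rule and would probably stop a gross device or motion fault. That also stands. QC material need not, however, reveal misses confined to patient blood, such as haemolysed samples, which K2 says can lower detection, or values near the cut point.

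Third, the comparator is a different assay, and K2 warns that absolute values vary between methods. A normal i-STAT result beside an elevated central result is therefore not always an i-STAT error.

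Fourth, a reader might infer that the rule contradicts the hypothesis in A2 that paramedics "will achieve 98% sensitivity and negative predictive value for MACE during the index visit and at 30 days". It does not. That target concerns the whole HEART assessment against MACE, which E2 and F3 measure directly, and wider use also depends on that result. But D4 does not make it part of the validation verdict, so the verdict still has no limit on missed elevations.

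**Conclusion.** The point holds as a weakness of the decision rule. Kappa > 0.74 is the only numeric pass mark for agreement, it is a point estimate blind to direction, and nothing in D4, F3 or K2 limits missed elevations. With 50 of 500 samples elevated, the patient-sample rule tolerates 26% to 38% missed as false-elevated results run from 9 down to 0. The one-quarter result does not need near-zero false elevations; the one-third result largely does. Both rest on an assumed share elevated and an assumed false-elevated rate.

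The consequence is limited. The protocol says that prehospital troponin results are not to be acted on during the pilot, so no decision in the pilot turns on this label. What is at stake is a validated verdict carried into later use on evidence that does not bound the relevant error. It is a cheap improvement, not a flaw in the primary analysis.

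**What to change.** In D4, report positive agreement (i-STAT elevated among centrally elevated) and negative agreement (i-STAT normal among centrally normal) beside kappa, each with the exact 95% interval that F3 already uses. Do not base the verdict on kappa alone. Then choose one of two routes:

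- Fix a minimum for positive agreement before the data are seen. The sponsor should choose it with the expected number of elevated samples and the assay difference in mind.
- Drop the validated verdict and let the estimates and intervals stand.

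A minimum should not be picked without checking how it behaves. As an illustration, requiring the exact lower bound to exceed 75% needs 24 of 25 (lower bound 79.6%; 23 of 25 gives 74.0%) or 44 of 50 (75.7%; 43 of 50 gives 73.3%). A device with true positive agreement of 90% would meet that only 27% of the time with 25 elevated samples and 77% with 50.

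The cost is a sentence or two in D4 and two proportions from the 2×2 table already planned, with no new samples. The downsides are a stricter rule that the device may fail, and wide intervals if few samples are elevated.
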